## Abstract

**Background:**

Hyponatremia is the most frequent electrolyte abnormality observed in post-operative pediatric patients receiving intravenous maintenance fluid therapy. If plasma sodium concentration (p-Na^+^) declines to levels below 125 mmol/L in < 48 h, transient or permanent brain damage may occur. There is an intense debate as to whether the administered volume (full rate *vs. *restricted rate of infusion) and the composition of solutions used for parenteral maintenance fluid therapy (hypotonic *vs. *isotonic solutions) contribute to the development of hyponatremia. So far, there is no definitive pediatric data to support a particular choice of parenteral fluid for maintenance therapy in post-surgical patients.

**Methods/Design:**

Our prospective randomized non-blinded study will be conducted in healthy children and adolescents aged 1 to 14 years who have been operated for acute appendicitis. Patients will be randomized either to intravenous hypotonic (0.23% or 0.40% sodium chloride in glucose, respectively) or near-isotonic (0.81% sodium chloride in glucose) solution given at approximately three-fourths of the average maintenance rate. The main outcome of interest from this study is to evaluate 24 h post-operatively whether differences in p-Na^+ ^between treatment groups are large enough to be of clinical relevance. In addition, water and electrolyte balance as well as regulatory hormones will be measured.

**Discussion:**

This study will provide valuable information on the efficacy of hypotonic and near-isotonic fluid therapy in preventing a significant decrease in p-Na^+^. Finally, by means of careful electrolyte and water balance and by measuring regulatory hormones our results will also contribute to a better understanding of the physiopathology of post-operative changes in p-Na^+ ^in a population at risk for hyponatremia.

**Trial registration:**

The protocol for this study is registered with the current controlled trials registry; registry number: ISRCTN43896775.

## Background

Hyponatremia, as defined by plasma sodium concentration (p-Na^+^) < 136 mmol/L, is the most common electrolyte abnormality in post-operative pediatric patients receiving parenteral maintenance fluid therapy [1]. Patients with hospital-acquired hyponatremia are exposed to major neurological complications if p-Na^+ ^declines to ~ 120 mmol/L in < 48 h [2].

Post-operative hyponatremia has been attributed to either an excess of delivered water or a net sodium deficit [1,3-5]. A series of pediatric investigations support the notion that a hospital acquired decrease in p-Na^+ ^in ill children receiving parenteral fluid therapy is the result of administering an excess of water relative to sodium, i.e., hypotonic saline solutions [6,7]. However, there is no definitive pediatric data to support a particular choice of parenteral fluid for maintenance therapy to prevent hyponatremia in either post-surgical patients or critically ill medical patients [8-10]. Therefore, data obtained by means of well-designed randomized clinical trials remains a pressing priority if uncertainties in the prescription of parenteral maintenance fluid therapy are to be resolved [11,12]. Based on previous lines of evidence, such an investigation should take into account the following facts: *i) *healthy kidneys are able to greatly vary the amount of water and sodium excreted to match the water and salt intake and therefore preserve the stability of the extracellular fluid compartment and maintain p-Na^+ ^within the physiological range [13,14], *ii) *conditions such as stress (e.g., pain, fever, and surgery), hypovolemia, vomiting, nausea, anesthesia, and intra-operative bowel manipulation are known non-osmotic stimuli for the production of antidiuretic hormone (ADH) [3,15-17], and *iii) *increased ADH levels impair the urinary dilution capacity and as a result free water retention in excess of sodium may ensue [18,19].

Taking this information into account, prescription of parenteral fluid therapy following a surgical intervention might pose a risk for a decrease in p-Na^+ ^whenever the kidneys lack the capacity to excrete an excess of water load [20,21]. Under such circumstances, hyponatremia would be the result of dilution of body solutes, i.e., an excess of water in relation to the existing sodium stores rather than to an increase in urinary sodium excretion. This suggests that after surgery, the prescription of parenteral maintenance fluid therapy should be tailored to the patient's water and electrolyte needs [22]. Indeed, in recent years it has been recommended to prescribe half the average of daily physiological losses as a measure to prevent post-operative hyponatremia [12,23,24]. This recommendation appears to be appropriate whenever the patient's extracellular fluid compartment is preserved and the urinary dilution capacity is suspected to be impaired by non-osmotic stimulated ADH activity [8].

Conversely, there is data supporting the view that hyponatremia might ensue due to desalination followed by the administration of intravenous replacement with hypotonic fluids [23]. It has been proposed that post-operative hyponatremia would be avoided by using isotonic saline instead of hypotonic saline for parenteral maintenance fluid therapy [11,25]. There is however no consensus as to whether or not the isotonic saline infusion rate should be restricted [11,25]. Notwithstanding this, a fall in p-Na^+ ^has also been also observed in surgical patients receiving near-isotonic saline infusions [26].

Based on existing pediatric data, it appears that tailoring post-operative parenteral fluid therapy to the individual patient's needs would be the most appropriate physiological approach, since no simple parenteral fluid therapy seems likely to be safely used in this clinical setting. Nevertheless, there is so far no study that suggests how this should be done.

At our hospital, the routine procedure for immediate post-operative parenteral maintenance fluid therapy consists of the use of near half-isotonic solution (0.40% salt solution, 70 mmol/L Na^+ ^+ 45 mmol/L Cl^- ^+ 25 mmol/L acetate in 2.5% glucose) given at low maintenance rate, i.e., at ~¾ the average maintenance rate. The administration of sodium acetate is intended as an alternative to NaCl as a source of sodium ion in a large volume infusion. In addition, acetate is an alternative source of bicarbonate by metabolic conversion in the liver. Although in our own experience (UF and [name], unpublished data), no patient treated in this way has experienced hyponatremia of potential clinical significance, defined as a fall in p-Na^+ ^fall < 130 mmol/L [27], our routine procedure does not rely on evidence-based medicine, but on theoretical grounds. Therefore, a well designed study seems warranted to determine the parenteral fluid regimen that can effectively and accurately be prescribed to post-operative pediatric patients [28]. In addition, logic-based evidence for appropriate laboratory monitoring is also justified.

In this paper, we detail our study protocol for a prospective randomized non-blinded investigation aimed at evaluating the efficacy of hypotonic and near-isotonic saline for parenteral fluid therapy given at low maintenance rate in post-operative pediatric patients, using p-Na^+ ^as a surrogate marker. Since at our Center acute appendicitis accounts for a large number of emergency surgical admissions, our investigation will be conducted in previously healthy children and adolescents who have undergone acute appendectomy for complicated appendicitis. The study will be started once the rationale behind this investigation as well as the full description of the protocol has reached the public domain. In so doing, we expect to receive comments that would eventually contribute to improve our protocol [29].

## Methods

### Objectives

Our primary outcome of interest is to evaluate whether the post-operative prescription of either hypotonic or near-isotonic fluid therapy given at low maintenance rate in otherwise healthy children with normal post-operative p-Na^+ ^are equally effective in maintaining p-Na^+ ^within the normal range. In addition, our secondary aim is to determine water and electrolyte-balance following the administration of the investigational parenteral maintenance fluids as well as to investigate known regulatory hormones involved in the homeostatic control of water balance. Finally, we will seek to determine how frequently p-Na^+ ^should be monitored during the post-operative period.

### Study Design

The present investigations will be set up as a prospective randomized non-blinded study. Eligible patients will be randomly assigned to receive one of the following electrolyte/glucose combinations as parenteral maintenance fluid therapies during the 24 h following surgery: *i) *0.23% sodium chloride (40 mmol/L Na^+ ^+ 20 mmol/L K^+ ^+ 60 mmol/L Cl^-^; extempore solution) in 5% glucose, *ii) *0.40% sodium chloride (70 mmol/L Na^+ ^+ 45 mmol/L Cl^- ^+ 25 mmol/L acetate; B. Braun Melsungen AG, Melsungen, Germany) in 2.5% glucose, or *iii) *0.81% sodium chloride (140 mmol/L Na^+ ^+ 4 mmol/L K^+ ^+ 1 mmol/L Ca^2+ ^+ 1 mmol/L Mg^2+ ^+ 118 mmol/L Cl^- ^+ 30 mmol/L acetate; Serumwerk Bernburg AG, Bernburg, Germany) in 1% glucose (the chemical symbols K^+^, Cl^-^, Ca^2+^, and Mg^2+ ^refer to potassium, chloride, calcium, and magnesium, respectively).

### Ethical Considerations

The study protocol has been approved by the Medical Ethics Committee at Karolinska University Hospital, Stockholm, Sweden (Protocol No. 2010/2:9). The study protocol was registered at current clinical trials registry database; http://www.controlled-trials.com/ISRCTN43896775, registry number: ISRCTN43896775).

A written and verbal version of the information will be presented to the potentially eligible patient and parents before the surgical procedure by the surgeon in charge of the patient. The exact nature of the study, the implications and constraints of the protocol, the known side effects, and any risks involved in taking part will be detailed. Parents and patients will be told that all study findings will be handled in strictest confidentiality and that it extends beyond the duration of the study. It will be clearly stated that the patient and parents are free to withdraw from the study at any time for any reason without prejudice to future care, and with no obligation to give the reason for withdrawal. Written informed consent will then be obtained by means of a dated patient's and parent's signature and dated signature of the surgeon who presented the informed consent form. A copy of the signed informed consent will be given to the patient.

### Study Population and Site

The participants will be recruited at the Department of Pediatric Surgery, Astrid Lindgren Children's Hospital, at the Karolinska University Hospital, Solna, Sweden. Potentially eligible participants in the study will be healthy children and adolescents consecutively operated for emergency abdominal surgery due to acute appendicitis.

Our Center is an academic teaching hospital that provides care in the majority of pediatric surgical cases in the greater Stockholm area, covering a population of about 1,8 million inhabitants, which corresponds to a referral area of approximately 350,000 children. More than 300 children and adolescents are admitted for treatment of acute appendicitis every year. The date for enrolment to the clinical trial will be defined once the protocol has reached public domain. The study will take place in the Pediatric Intensive Care Unit, Astrid Lindgren Children's Hospital, at the Karolinska University Hospital, Solna, Sweden.

### Eligibility Criteria

In the present investigation, we arbitrarily decided not to include children aged less than 1 year of age because the functional capacity of the kidney, including glomerular filtration rate and renal concentration ability, as well as the efficiency to excrete sodium load is lower in infants than in older children [30-33]. Hence, the study population will be male and female children and adolescents aged between 1 and 14 years old whose post-operative p-Na^+ ^are within the normal range (local reference range: 135 - 147 mmol/L). Children and adolescents undergoing emergency intervention for treatment of acute appendicitis either as an open or laparoscopic procedure will be considered to be potentially eligible. To qualify for randomization, the participants are required to have a complicated appendicitis, i.e., gangrenous or perforated, either with generalized or localized peritonitis of such a degree that the surgeon considers oral feeding unsuitable for at least 24 h following the surgery. Consequently, the randomization will be performed post-operatively and on the basis of intra-operative findings.

We infer that in our study population, the prescription of parenteral fluid therapy for the immediate 24 h post-operative period might be justified, and that by delaying oral fluid therapy intake, in any particular case, will do no harm to the patient.

The exclusion criteria will be any clinical condition, such as renal disease, acute or chronic lung inflammation, pituitary or hypothalamic disease, and adrenal insufficiency that eventually can lead to electrolyte and water imbalance. In addition, any patient whose p-Na^+ ^is < 130 mmol/L after the initiation of parenteral maintenance fluid therapy, will be withdrawn from the study and treated accordingly at the discretion of the anesthesiologist responsible for the patient's care [34].

Whenever the occurrence of vomiting is reported or if the patient complains of symptoms attributable to symptomatic hyonatremia such as nausea, malaise, headache, restlessness, drowsiness, or decreased consciousness, p-Na^+ ^will be immediately controlled and the event clearly documented in the medical record.

During the first 24 h post-operatively, the administration of extra fluid besides the study maintenance fluid therapy, will be not permitted with the exception of fluid administered with medication or to maintain patency of peripheral intravenous catheters.

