### Clinical and Laboratory Assessment

Upon admission from surgery and by the end of the first post-operative day, patients will be weighted (kg). In addition, height (m) will be measured and body mass index (kg/m^2^) calculated. Non-invasive blood pressure (mm Hg), heart rate (beats per minute), monitoring of arterial oxygen saturation with pulse oximetry, and body temperature will be recorded at regular intervals.

Blood samples will be collected immediately after the conclusion of surgery (T_0_), at 6 h (T_6_) and 12 h (T_12_), and then at 24 h (T_24_) following the surgery. The blood samples obtained at T_0 _and T_24 _will be analyzed for plasma (p) Na^+^, K^+^, Cl^-^, creatinine, urea, uric acid, glucose, lactate, ketones, renin, aldosterone, ADH, hemoglobin, blood gas, and for serum (s) osmolality by means of routine and quality controlled laboratory techniques. Serum Cortisol and s-TSH (thyroid-stimulating hormone) will be measured at T_0_. At T_12_, p-Na^+^, p-glucose, and blood gas will be monitored. The blood samples obtained at T_6 _and T_12 _will be analyzed for p-Na^**+**^. Also, at the discretion of the treating anesthesiologist, p-Na^+ ^will be monitored at intermediate sampling if p-Na^+ ^at T_12 _follows a decreasing trend.

Entire urine collection from T_0 _to T_24 _will be obtained by urine bag or clean catch, as appropriate. A bladder scan will be performed whenever urinary retention is suspected. Depending on the bladder volume measured, urethra catheterization will be performed to relieve urine retention if the patient cannot void on his/her own. Adequacy of timed urine collection will be confirmed as far as possible by estimation of urinary creatinine excretion rate (mmol/kg per 24 h) [35].

In addition to measuring total urine volume, urinary sodium, potassium, and chloride excretion, we will calculate, from spot urine samples obtained at T_0 _and T_24_, the fractional excretion of sodium (FeNa), the fractional excretion of uric acid (FeUA), and the urine osmolality.

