#### Sample size calculation

The expected sample size required in our study is based on the calculation for equality applied to the primary outcome variable p-Na^+^, measured at T_24 _as mmol/L.

In the previous section we estimated that the largest expected fall in p-Na^+ ^in our illustrative case would be 3.6 mmol/L. Consequently, if we apply this figure to a patient whose p-Na^+ ^at T_0 _is 135 mmol/L, the expected p-Na^+ ^at T_24 _after giving 0.4% sodium chloride would be 131.4 mmol/L, a plasma level which may not have clinical significance [27]. However, we are compelled to speculate that this figure may not be exact because in our illustrative case we dealt with hypothetical data that may not necessary mirror the clinical setting. Hence, our estimate has to be verified by means of water and electrolyte balance measurement *in vivo*. Taken this uncertainty into account, we arbitrarily decided that the equality margin will be set at 5 mmol/L. This value will capture our estimate, but, most importantly, in patients whose p-Na^+ ^at T_0 _is 135 mmol/L, it would allow us to identify those patients who are at risk for developing hyponatremia of potential clinical significance [27]. Thus, a difference between treatment groups greater than this margin will be considered as clinically relevant. Consequently, a difference smaller than 5 mmol/L will be considered as clinically less relevant. Sample size was calculated assuming a standard deviation (SD) of 5 mmol/L, a significance level of 0.05, and a power of 80% to detect a difference larger than the equality margin of 5 mmol/L. Hence, the number of patients per study arm needed to fulfill the power goal of the study will be 17 patients.

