#### Data analysis

All statistical analyses will be described in detail in the statistical analysis plan. Data will be presented using descriptive statistics, i.e., mean and SD for continuous variables, and frequency and proportions for categorical variables. The efficacy variable will be evaluated using ANCOVA, intervention (parenteral maintenance fluid therapy) as a fixed factor and baseline levels as a covariate in the model. The corresponding 95% confidence intervals for each group and the difference between groups will also be presented. In addition, graphs will be used in order to facilitate the interpretation of the results regarding the equality margins to be used in the present study.

Missing data will be replaced using a conservative approach, which will be specified in the statistical analysis plan. All tests will be two-sided and performed at the significance level of 0.05.

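### Withdrawing a child from the study when p-Na falls below 130 mmol/L selects on the primary outcome variable and risks biasing the comparison toward equality

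*Protocol article*

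**What the plan says.** All references are to the protocol article.

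- **Eligibility Criteria.** In the paragraph on exclusion criteria, a child with p-Na below 130 "mmol/L after the initiation of parenteral maintenance fluid therapy, will be withdrawn from the study and treated accordingly". The child leaves the study, not only the study fluid, and the rule has no upper time limit. Entry requires a post-operative p-Na of 135 to 147 mmol/L.
- **Objectives.** The question is whether the fluids "are equally effective in maintaining p-Na" in the normal range.
- **Sample size calculation.** The size is "based on the calculation for equality applied to the primary outcome variable p-Na" at T24. On the margin: "we arbitrarily decided that the equality margin will be set at 5 mmol/L". Its justification is that, for a child starting at 135, "it would allow us to identify those patients who are at risk for developing hyponatremia of potential clinical significance".
- **Clinical and Laboratory Assessment.** p-Na is scheduled at T0, T6, T12 and T24 in every arm. Intermediate samples are taken "at the discretion of the treating anesthesiologist" when T12 shows a downward trend.
- **Analysis population.** Intention to treat covers every randomised child who received a study fluid, but the analysis is then confined to those free of violations or deviations.
- **Data analysis.** "Missing data will be replaced using a conservative approach", with the method deferred to the SAP. The primary model is an ANCOVA with baseline as covariate.

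**The concern.** A rule that removes children after randomisation because of their own p-Na makes the remaining sample depend on the outcome. The margin reaches down to 130 for a child who starts at 135 (135 − 5 = 130), so the children it is meant to flag are those the rule sends out of the study.

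The direction matters because the trial asks about equality. The protocol's worked example predicts T24 values of 136.5 and 136.4 mmol/L on the hypotonic fluids and 138.2 on the near-isotonic one. If the hypotonic arms have more falls below 130, they lose more low values, their remaining mean rises, and the contrast with the near-isotonic arm shrinks. That favours a conclusion of equal effectiveness. Little distortion is expected between the two hypotonic arms, whose predicted means are almost the same.

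The withdrawn children are also the most informative for the secondary aims: water and electrolyte balance, regulatory hormones, and how often p-Na should be monitored. An SAP cannot recover samples that the protocol did not have taken.

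**Working it through.** **Step 1: the plan's own figure.** The inputs are "assuming a standard deviation (SD) of 5 mmol/L, a significance level of 0.05, and a power of 80" percent, two-sided, difference 5. The normal approximation gives n = 2 × (1.960 + 0.842)² × 5² / 5² = 15.7, so 16 per arm. The t-test version gives 16.7, so 17, with 80.7% power. The stated 17 is reproduced, and it assumes that no outcome is selectively lost.

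**Step 2: inputs for the effect of the rule.** From the protocol: cut-off 130, T0 within 135 to 147, SD 5, difference 5, near-isotonic T24 mean 138.2. Assumptions of this review:
- comparator T24 mean 138.2 − 5 = 133.2
- SD also tried at 3
- T0 mean 140 or 138.2
- linear fall, so mean at time t = T0 mean − (total fall) × t/24
- correlation 0.5 or 0.7 between successive samples
- analysis of the remaining children only, with no replacement

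**Step 3: hand check with every T24 value below 130 removed, SD 5.** For a normal variable, E[X | X > c] = μ + σ·φ(a)/(1 − Φ(a)), with a = (c − μ)/σ.
- μ = 133.2: a = −0.64, Φ = 0.261, φ = 0.325. Mean = 133.2 + 5 × 0.325/0.739 = 135.40.
- μ = 138.2: a = −1.64, Φ = 0.051, φ = 0.104. Mean = 138.2 + 5 × 0.104/0.949 = 138.75.
- Difference = 138.75 − 135.40 = 3.35 instead of 5.0.

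With SD 3, 14.3% and 0.3% are removed and the difference is 138.23 − 133.99 = 4.24.

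**Step 4: simulation of T0, T6, T12 and T24 with the entry limit on T0.** True difference 5.0.

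| Trigger for removal | SD | Removed, lower arm | Removed, near-isotonic arm | Difference left |
|---|---|---|---|---|
| T6 or T12 below 130 | 5 | 8–13% | 3–6% | 4.7–4.8 |
| T6 or T12 below 130 | 3 | 1–3% | under 0.5% | 4.9–5.0 |
| T6, T12 or T24 below 130 | 5 | 24–31% | 6–9% | 3.4–3.6 |
| T6, T12 or T24 below 130 | 3 | 12–15% | under 1% | 4.2–4.4 |

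At the smaller gap in the protocol's example (138.2 − 136.4 = 1.8, SD 5), T6/T12 withdrawal leaves about 1.7. Every scenario moves the difference toward zero.

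**Step 5: effect of the remedy.** In the same simulation, using the triggering value for children withdrawn at T6 or T12, and keeping all T24 values obtained, gives 4.9 to 5.0.

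**Step 6: how common the event is, on the protocol's evidence.** Background reports no such fall in the centre's experience with the 0.40% fluid. The Discussion reports none at 24 h in a recent randomised trial and none in a prospective series on full-rate hypotonic fluid. Against this, a retrospective series had 16 of 145 = 11%. At that rate an arm of 17 would have 0.11 × 17 = 1.9 such children.

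**The case against.** The strongest reply is that the protocol never says these children are left out of the analysis. They meet its intention-to-treat definition, a withdrawal that the protocol itself prescribes is not obviously a deviation, and missing values are to be replaced. Carrying the low value forward would be conservative here and close to the remedy proposed below, and the unseen SAP may specify it. This stands: a reader might infer that the worst outcomes will certainly be lost, and the documents support only a risk. It does not remove the point. Whether sampling continues after withdrawal is a protocol matter, and in a trial of equality a replacement that draws the arms together would not be conservative.

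A reader might also take 3.4 mmol/L as the expected result. That needs a T24 value already in hand to be discarded. The open-ended wording permits this, but nothing states it, and by T24 the infusion period is over.

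A reader might infer a plain loss of power from fewer children per arm. Equal losses in each arm do not follow from a mechanism that works through unequal ones, so no such claim is made.

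Nor do the discretionary samples show much unequal detection, although the team knows the allocation. T6 and T12 are scheduled for all, checks after vomiting or symptoms are required, and discretion covers only extra samples after a falling T12.

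Finally, events may be rare. In the one series with a notable rate, incidence was similar on hypotonic and isotonic fluid, and most cases received about full maintenance or more. This limits the likely size, but does not justify selecting on the outcome.

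**Conclusion.** The point holds as a flaw in a stated rule. Study withdrawal depends on the primary outcome variable, and the text secures neither the triggering value nor later data. The bias runs toward equality provided that falls below 130 are commoner on hypotonic fluid, as the worked example implies. Under the assumptions in the working, a true 5 mmol/L becomes about 4.7 to 5.0 with withdrawal at T6 or T12, and about 3.4 to 4.4 only if low T24 values are dropped as well. The documents do not fix the size. With zero or one event per arm it would be slight; with a few among 17, clustered in the hypotonic arms, it could matter. Confidence is high on the mechanism and low on the magnitude.

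**What to change.** Leave the child's care and the 130 mmol/L threshold as they are, and separate them from study participation:

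1. State in Eligibility Criteria that a child with p-Na below 130 stays in the study for data, including T24 blood and the urine collection, and stays in the intention-to-treat analysis.
2. In the primary ANCOVA, use the last p-Na before corrective treatment as that child's outcome. Keep any T24 value below 130 obtained without prior corrective treatment.
3. Report the number of children below 130 in each arm.
4. As sensitivity, fit a repeated-measures model to T6, T12 and T24 with T0 as covariate, so that values before withdrawal contribute.

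The cost is about one sentence in the protocol and a short addition to the analysis text, and the samples are already scheduled. The downside is that the outcome time for these children is earlier than T24, which the report should say. Background states that the study will start only after publication and that comments are expected, so the change can be made before enrolment.
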